**CHARACTERISTIC MEASURES AND EFFECT MODIFIERS**		
Demographics	Standardised Demographics Questionnaire (SDQ) (10-items)	
Personality disorder symptoms	Personality Disorder Severity Scale (PDS-ICD-11) [36] (14-items)	
Mood-related quality of life	Mental Health Recovery Measure (MHRM-10) [37] (10-items)	
Socioeconomic constraints	American Academy of Family Physicians - Social Needs Screening Tool [38] (15-items)	
Medication adherence	Medication Adherence Reporting Scale (MARS-5) [39] (5-items)	
Readiness to make changes in behaviour prior to the intervention	Readiness to Change Questionnaire (RCQ) [40]	
Treatment expectancy and rationale credibility	Credibility Expectancy Questionnaire (CEQ) [41] (6-items)	
Presence of major depressive episode, and diagnosis of major depressive disorder or bipolar affective disorder	The Structured Clinical Interview for DSM-5 (SCID-5)	

Secondary outcome measures address a range of mood, quality of life, functional recovery outcomes and lifestyle related outcomes (see Table 3) and are collected during the video interviews conducted at baseline and 8-week follow-up.

#### Safety measures

Participants complete weekly questionnaires via email including an adverse events questionnaire that investigates both mood-related and non-mood related changes to health, and the Depression Anxiety Stress Scale – 10 (DASS-10) [42] to assess participants’ levels of psychological distress. The DASS-10 consists of 10 items to measure depression, anxiety and stress. Respondents rank on a 4-point scale the extent to which they have experienced symptoms of depression, anxiety, or stress over the past 7 days, from 0 “Never” to 3 “Almost Always”. Scores range from 0 to 30, with higher scores indicating more severe psychological distress. DASS-10 scores exceeding 13 or increasing by 0.5 standard deviations or more since the previous week trigger facilitator follow-up with participants for further details and clarification. Trial medical personnel are consulted for resulting actions, such as escalation of care, where necessary. Adverse events and their severity, likely relatedness to the intervention or trial involvement are classified using the Medical Dictionary for Regulatory Activities (MedDRA) classification system and are further adjudicated by an independent mental health physician.

A Data Safety Monitoring Board (DSMB) chaired by a medical professional specialising in psychiatry oversees the safety and progress of the trial by providing recommendations about continuing, modifying, or stopping the trial. The DSMB members provide expertise in psychiatry, biostatistics, behavioural science, psychology, epidemiology, and clinical trials. The DSMB is responsible for safeguarding the interests of trial participants by assessing the safety of the interventions during the trial, and the general stewardship and progress of the trial, amongst other responsibilities. The DSMB review trial data 6 months after trial commencement, and then annually with blinded interim analysis data presented mid-way through the trial. Serious adverse events are reported to the DSMB and Human Research Ethics Committee (HREC) within 24 h.

#### Intervention adherence and integrity

Participant completion of the intervention is defined as attendance of 50% or greater (more than 4 out of the 7 total sessions). Participant attendance at every group session is recorded by the facilitators.

To assess participant adherence to the dietary component of the lifestyle program, participants are provided with the HARMON-E Diet Weekly Checklist to complete at week 1 and week 7. While quantitative scores on the checklist are not directly discussed with participants as this may undervalue their efforts or achievements, dietitian facilitators use the data to promote general discussion about dietary intake and encourage behaviour change. Participant adherence to the physical activity aspect of the lifestyle program is monitored weekly via the Simple Physical Activity Questionnaire (SIMPAQ) and Borg scale [34, 35] to gather physical activity duration and intensity data which will shape the group conversation.

All sessions are recorded on online videoconferencing platform Zoom, and 10% of these recordings are reviewed for fidelity by assessing group facilitator adherence to pre-specified session content. Fidelity is assessed by two independent research staff members (one with qualifications related to each condition). Further, Zoom-based polls comprising five questions with Likert-scale responses will be conducted at the end of each session, which will provide participants with the opportunity to give feedback on the contents and conduct of each session. This information will be used for outcomes such as process evaluation and enhancing participant engagement.

### Study conditions

Both arms are matched in terms of frequency, intensity and scheduling. This includes 7 sessions over 8 weeks comprising a one-on-one session and six group sessions. Details of the session content are provided below:

#### Lifestyle therapy program

The lifestyle program is cofacilitated by a dietitian and an exercise physiologist and aims to (i) enhance daily lifestyle management for those living with major depression and bipolar disorder, (ii) improve social and emotional support through lifestyle-based goal attainment, and (iii) improve links to ongoing and pre-existing clinical/other supports to help maintain lifestyle modification in the long term.

The program’s content builds on that developed for the CALM trial (the development of which has been published and described elsewhere [10, 43]), but goes beyond diet and physical activity to include sleep hygiene, and substance use (including alcohol, smoking, and drug use). See Table 4 for a summary of program objectives. Meta-analytic data suggests that lifestyle interventions that target multiple pillars are likely to be more successful in the treatment of depression than single-focused lifestyle interventions [7, 43, 44]. Moreover, our experiences of the CALM trial suggested that nutritional counselling often indirectly includes discussion of alcohol and other substances and similarly exercise counselling can indirectly include discussion of sleep and sedentary behaviour.

**Table 4 Tab4:** Intervention program objectives

**Lifestyle arm**	
Diet	• Enjoy a wide variety of nutritious foods • Select a variety of healthy high-fibre plant foods • Include good quality fats • Limit discretionary foods to special occasions only
Physical activity	• Participate in enjoyable physical activity
Sleep	• Aim for 7–9 h of sleep a per night
Substance use	• Have no more than 2 standard alcoholic drinks on one occasion and no more than 10 standard drinks per week • Manage your use of and harm associated with tobacco and other substances
**Psychotherapy arm**	
	• Understand triggers and factors that contribute to low mood • Engage in a range of soothing and activating practices and notice the impact on mood • Identify personal values and use these to develop goals • Develop an awareness of feelings and practice naming and describing them • Engage in regular practice of relaxation or mindfulness exercises • Identify thinking patterns and notice how these influence mood and behaviour • Develop a more balanced way of thinking about situations • Use behavioural experiments to face up to challenging situations • Develop a relapse plan for managing mood long term

Program goals for the lifestyle arm are defined as (i) at least a 15% improvement on “HARMON-E Diet” score (used to assess how closely participants are adhering to a modified Mediterranean diet) by 8 weeks, (ii) a reduction in participants’ risk profile category on the Alcohol, Smoking and Substance Involvement Screening Test (ASSIST) [30] questionnaire (alcohol section) by 8 weeks, (iii) a reduction in participants’ risk profile category for at least one substance on the ASSIST questionnaire (substances section) by 8 weeks, (iv) a reduction in participants’ insomnia severity profile category on the Insomnia Severity Index (ISI) [28] questionnaire by 8 weeks, and (v) achieved the Australian physical activity guidelines of 150 min of moderate intensity or 75 min of vigorous intensity physical activity per week, ascertained through data from the SIMPAQ and Borg scales at 8 weeks.

The lifestyle program is manualised to allow for replication and to promote fidelity, however, it has the flexibility to allow participant discussion to guide content and to be tailored to the individual needs of the group. Example activities during the group sessions include creating balanced meals, key nutrients and foods for mental health, mindful eating, finding enjoyable physical activity in different contexts, practical physical activity examples, tips for improved sleep, and discussion of alcohol management. Participants are encouraged to set goals in each session to support behaviour change.

Participants are provided an AUD$50 grocery shopping voucher to promote adherence to dietary improvements and a 1-metre TheraBand™ as a convenient alternative to free weights to encourage participation in resistance training exercises, during and outside of group sessions. A workbook is provided in both hard and digital copy formats, which outlines content covered during the session as well as information for further learning between sessions.

#### Psychological therapy program

Two registered psychologists with specialised clinical training, or a provisional psychologist in a clinical training program under the supervision of a senior clinical psychologist, co-deliver the psychological intervention using a CBT approach. This is the current gold-standard treatment for depression and anxiety and can be successfully delivered remotely [45] and in a group setting [46]. The program (objectives summarised in Table 4) is based on international evidence-based practice guides [47, 48] and incorporates feedback from the trial’s lived experience project officer.

Facilitators use similar techniques to that of the facilitators of the lifestyle arm such as goal setting and aspects of motivational interviewing, but differ by applying Socratic questioning and cognitive restructuring techniques throughout the sessions. Each session begins and ends with a mindfulness exercise to promote emotional regulation during and between sessions. Session content includes foundational CBT skills such as identifying and naming feelings, behavioural activation, identifying unhelpful thoughts, thought disputation, and behavioural experiments. The final session focuses on relapse prevention and self-management. In an attempt to minimise contamination across arms, facilitators do not promote discussion of the lifestyle-based goals being covered in the lifestyle therapy arm as part of CBT but cover other areas which can be considered related to lifestyle if they arose (e.g. social support, mindfulness).

Program goals in the psychological therapy group are assessed using the CBT Suitability Scale (CBT-SUITS) [49], which is a measure of attitudes aligned with CBT. These include (i) a 10% improvement for the CBT-SUITS total score, (ii) a 10% improvement for the rationale subscale, (iii) a 10% improvement for the insight subscale, and (iv) a 10% improvement for the behaviour subscale. Whilst designed as a measure of CBT suitability and attitudes, scores on this measure have been found to relate to post-treatment symptoms and distress. In particular, the insight subscale uniquely predicted post treatment change even when controlling for baseline scores [50].

To create parity in engagement between the intervention arms, psychological therapy participants receive a “Self-Soothe Hamper” valued at AUD$50, which includes an acupressure ring, head massager, stress ball, mental health services magnet, key ring, and a deck of CBT cards. These items were chosen to promote engagement and suitability during and after the intervention. Like the lifestyle intervention, a workbook is provided in both hard and digital copy formats, which outlines content covered during the session and promotes engagement in activities outside of sessions.

Lived experience representatives at both project team level and Steering Committee level provide lived experience perspectives into the development and implementation of both program arms, such as reviewing workbook contents and layout, and recommendations for sequence of session contents for both arms.

#### Blinding and randomisation

As this is a single blind trial and participants cannot have their allocation concealed, they are asked to conceal the condition to which they have been assigned during all follow-up assessments. Baseline assessments are conducted by blinded research assistants prior to participant’s randomisation and commencement of either program. Blinding of research assistants is maintained through restricted access to unblinded sections of the database. Blood collection is completed in-person by blinded phlebotomists.

Upon enrolment, participants are assigned a unique study identification (ID) number for randomisation and data collection purposes. Randomisation occurs when a sufficient number of participants (minimum of *n* = 4 per treatment arm) have completed their baseline assessments. Participant allocation to either arm is done through permuted block randomisation in a 1:1 ratio (intervention to control), which is conducted by an independent statistician. On the day of randomisation, the statistician emails the allocation sequence for each group to the trial coordinator who assigns participants to their program. This process conceals the sequence prior to participants’ program allocation.

The interim analysis is conducted by an unblinded biostatistician, and the final analysis will be performed by a biostatistician who is blinded to treatment allocation.

### Data analyses

A comparison of baseline measures and demographic variables across allocation arms will be conducted to ensure the treatment arms are well balanced. Further, a comparison of drop-out rates across allocation arms will also be carried out and variables associated with drop-out will be identified using binary logistic regression analysis. A three-level hierarchical linear model analysis (or multi-level model analysis) will be conducted for all primary and secondary outcome measures, allowing for correlations within treatment groups (level 3) and individual participants (level 2) and repeated measurements over time (level 1). Changes between baseline and the primary endpoint (8-weeks) (continuous outcomes on the MADRS) will be presented as an Intention-To-Treat (ITT) and Per Protocol analyses with the greatest confidence for non-inferiority occurring when results between analysis sets are concordant. Any demographic variables associated with allocated arm or drop-out rates will be controlled for. Finally, follow-up analyses will be conducted for primary and secondary measures, again using a three-level hierarchical linear model analysis.

Consistent with ICHe9(R1) and the pragmatic approach adopted in this trial, a treatment policy estimand will be applied throughout. Thus, all data regardless of anticipated intercurrent events (e.g., missed assessment sessions, treatment discontinuation) will be analysed. Wherever possible, missing data will be imputed using pattern mixture modelling under the assumption of Missing Not at Random. Sensitivity analyses will be conducted to assess the effect of missing data and differences between ITT and per-protocol populations.

An interim analysis will be conducted following 50% recruitment. The intention of this analysis will be to assess efficacy and futility, along with safety considerations to inform trial cessation.

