### Recruitment

Recruitment is being conducted from September 2022 to April 2025. Participants are recruited through General Practice (GP) and community-based advertising. GP recruitment is conducted in partnership with established Practice-based Research and Education Networks to recruit participants presenting to their GP with depression or bipolar affective disorder.

Community-based recruitment uses mediums such as social media advertising, pamphlet distribution in pharmacies, gyms, universities, and other locations frequented by the general population. Further, detailed presentations will be provided by research staff to outpatient mental health services to suggest the study to their consumers who may benefit from participation. The wording of recruitment material is neutral and does not mention the nature of the interventions (referred to as ‘mental health programs’) to reduce expectation bias.

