### Sample size

A Minimal Clinically Important Difference (MCID) for the MADRS primary outcome measure has been shown to be 1.6–3.0 [16–20], therefore the non-inferiority margin was set at < 1.6.

Power analysis was conducted to analyse the non-inferiority hypothesis of between group mean difference greater than the Minimal Clinically Important Difference. Several assumptions were made including a MCID on the MADRS = 1.6 [16], a Standard Deviation (*sd*) of change in MADRS scores from baseline to week 8 = 3.6 (baseline variance = 4.03) were assumed, resulting in a total sample size of 126. An Intraclass Correlation Coefficient = 0.2 was used to account for variation between therapy groups with an average size of 8 per group. A conservative level of attrition = 20% was further assumed.

Using the formula from Van der Weele et al. [21], the Design EFFect (DEFF) for *n* = 8 participants per therapy group, the final sample was therefore 126*2.4/0.8 = 378 with 189 participants per arm.

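### The three-level model omits the randomisation batch, so any variation shared by the two arms of a batch makes the reported standard error too large and the non-inferiority interval conservative

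*Protocol article*

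**What the plan says.** **Allocation.** Under Blinding and randomisation the protocol states: "Randomisation occurs when a sufficient number of participants", defined as at least 4 per arm, have finished baseline. They are then allocated 1:1 by permuted blocks. Baseline assessments precede randomisation.

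**Calendar.** "Recruitment is being conducted from September 2022 to April 2025", which is 32 calendar months counted inclusively. Study conditions says that the arms are matched on scheduling, and Table 2 puts both on one timetable from Week 0. A simultaneous start of the two groups of a batch is implied, not stated.

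**Model.** Data analyses specifies a three-level hierarchical linear model for primary and secondary outcomes, "allowing for correlations within treatment groups (level 3) and individual participants (level 2) and repeated measurements over time (level 1"). The only further covariates named are demographic variables associated with arm or drop-out. Batch, calendar time and waiting time do not appear.

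**Planning figures.** Sample size gives the margin ("therefore the non-inferiority margin was set at < 1.6"), the SD ("of change in MADRS scores from baseline to week 8 = 3.6 (baseline variance = 4.03) were assumed"), the unadjusted size ("resulting in a total sample size of 126") and the clustering assumption ("Intraclass Correlation Coefficient = 0.2 was used to account for variation between therapy groups", "with an average size of 8 per group").

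**The concern.** Each batch acts as a randomisation stratum that supplies therapy groups to both arms. Batches can differ in season, in calendar time and in the average wait between baseline and Week 0. Because baseline is measured before randomisation, the wait falls inside the baseline-to-week-8 change that forms the primary outcome.

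To the extent that such influences act alike on both arms of a batch, they drop out of the arm difference. The stated model does not know which therapy groups belong together. It treats them as independent and books the shared part as group-to-group variance, which enters the standard error of the arm difference.

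Non-inferiority is decided by an interval against a narrow 1.6-point margin. An interval wider than the design warrants could leave a trial of a truly non-inferior therapy inconclusive.

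**Working it through.** **1. Reproduce the plan's size.** The article does not state alpha and power. One-sided 5% and 80% are inferred because they return the plan's figure:

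n per arm = 2 × (1.645 + 0.842)² × 3.6² / 1.6² = 62.6, rounded up to 63, so 126 in total. (One-sided 2.5% would give 160 at 80% power.)

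Design effect = 1 + (8 − 1) × 0.2 = 2.4, and 126 × 2.4 / 0.8 = 378, as stated.

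Planned SE = 3.6 × √(2/63) = 0.641. Planned power = Φ(1.6/0.641 − 1.645) = 80.2%.

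**2. Split the ICC.** Let a share w of the 0.2 be common to both arms of a batch. No figure in the protocol fixes w, so it is an assumption. In units of the total variance, a therapy-group mean has variance 0.2 + 0.8/8 = 0.3 as modelled. Only 0.3 − 0.2w of it reaches the arm contrast.

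- SE ratio, reported to true = √(0.3 / (0.3 − 0.2w))
- True SE, also the SE reported with a batch term = 0.641 / ratio
- Power without a batch term = Φ((1.6 − 1.645 × 0.641) / true SE)
- Power with a batch term = Φ(1.6 / true SE − 1.645)
- Implied between-batch SD = 3.6 × √(0.2w)

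| w | Between-batch SD (MADRS points) | Reported SE, no batch term | True SE | SE overstated by | Power without | Power with |
|---|---|---|---|---|---|---|
| 0 | 0 | 0.641 | 0.641 | 0% | 80% | 80% |
| 0.10 | 0.51 | 0.641 | 0.620 | 3.5% | 81% | 83% |
| 0.25 | 0.80 | 0.641 | 0.586 | 9.5% | 82% | 86% |
| 0.50 | 1.14 | 0.641 | 0.524 | 22% | 85% | 92% |

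At w=0.5, a nominal two-sided 95% interval uses 1.96 × 1.225 = 2.40 true standard errors and covers 98.4%.

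**3. Simulation.** The formula ignores the degrees of freedom that a batch term uses, and it keeps 8 per group after attrition. The check used 24 batches (378/16 = 23.6), one group per arm, 8 × 0.8 = 6.4 completers per group, and 20,000 runs. Group means were compared unpaired and then paired by batch.

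| w | True SD of contrast | Mean SE without / with batch | One-sided type I error without / with (nominal 5%) | Power without / with |
|---|---|---|---|---|
| 0 | 0.593 | 0.589 / 0.586 | 4.9% / 5.0% | 84.6% / 83.6% |
| 0.25 | 0.544 | 0.589 / 0.539 | 3.8% / 5.1% | 86.3% / 88.4% |
| 0.50 | 0.490 | 0.589 / 0.487 | 2.5% / 4.9% | 88.7% / 93.4% |

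Base power exceeds 80% here because attrition shrinks the groups rather than removing whole ones: 3.6 × √(2 × (0.2 + 0.8/6.4)/24) = 0.592, against 0.641 in the plan.

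A small mixed-model simulation (150 runs, uneven group sizes) gave the same pattern at w=0.25: mean SE 0.600 without batch and 0.557 with it. It is too small to confirm the true SD, and the runs at higher w did not finish.

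**4. Batch variance on top of the ICC.** If the 0.2 excludes batch variation, the true SE stays at 0.641 and the reported SE rises to 0.641 × √((2.4 + 8r)/2.4) for an extra batch ICC of r.

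- r=0.05: SE overstated by 8.0%; power without a batch term = Φ(2.494 − 1.645 × 1.080) = Φ(0.718) = 76%
- r=0.10: SE overstated by 15.5%; power = Φ(2.494 − 1.645 × 1.155) = Φ(0.595) = 72%

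By the same formula, a batch term restores 80.2%.

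**The case against.** The case for leaving the model alone has real weight.

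- **Direction.** A reader might infer bias, a truly noisier contrast, or a raised risk of falsely claiming non-inferiority. The design supports none of these. With 1:1 allocation within batches the shared part cancels, the true SD of the contrast falls as w rises, and type I error drops below nominal. This objection stands in full.
- **Power.** A reader might infer an underpowered trial. When batch variance is part of the 0.2, the sample size has already paid for it, and every power figure without a batch term is at or above 80%. What is lost is an available gain. A shortfall arises only in the case of step 4.
- **Size.** The protocol gives no seasonal, batch or waiting-time variance. Shares much above 0.5 would put the between-batch SD near the margin itself (w=0.75 gives 3.6 × √0.15 = 1.4 points), and nothing in the protocol supports that. This stands, so the result is a range and not an estimate.
- **Premises.** Parallel starts are inferred from matched scheduling, and equal action on both arms is assumed. Waits also vary between people within a batch, and a batch term leaves that part in place.
- **Unit of randomisation.** Participants are individually randomised, and therapy group at level 3 is the clustering that this design creates. The model is therefore not wrong about the unit. It leaves out the stratum within which that unit is allocated.
- **Left to the analysis plan.** A plan not shown here may add batch, and three named levels do not forbid a fixed covariate. But the article is not silent on the model. It fixes the levels and the rule for covariates, and as written these treat paired therapy groups as unrelated.

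**Conclusion.** The point holds as one of efficiency, not validity. The stated model ignores the batches in which participants are randomised, so its standard error is too large whenever the two arms of a batch share variation. The arm estimate is unbiased, and a non-inferiority finding from the model would be conservative.

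If 10% to 50% of the planned ICC is due to batch, the overstatement is 3.5% to 22%. At shares of 0.25 to 0.5 the forgone power is about 2 to 5 points in simulation and 4 to 7 by formula. At a share of zero nothing is lost.

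These figures rest on an assumed batch share, roughly balanced arms within each batch, parallel starts, and an inferred one-sided 5% alpha with 80% power. It is worth correcting because the remedy is cheap and the conclusion depends on the width of one interval.

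**What to change.** Add randomisation batch to the primary and secondary models, preferably as a random effect with therapy groups nested in batch by arm; a fixed stratum effect is the alternative. State this in the analysis plan before the final analysis. Keep the batch number and the days from baseline to Week 0 in the analysis dataset.

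The cost is one model term, using batch membership already known from the randomisation dates. If batch variance is zero, the lost degrees of freedom cost about 1 point of power (84.6% against 83.6% in the simulation). The term does not remove differences in waiting time between participants of the same batch.

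### The three-level model places therapy group above baseline as well as week 8; if level 3 is a random intercept, the clustering drops out of the change contrast and the primary interval is too narrow

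*Protocol article*

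**What the plan says.** - **Model.** Data analyses specifies a three-level hierarchical linear model for all primary and secondary outcomes, "allowing for correlations within treatment groups (level 3) and individual participants (level 2) and repeated measurements over time (level 1"). The primary result is the MADRS change between baseline and 8 weeks. No random intercept, random slope or other random term is named.
- **Timing.** Under Blinding and randomisation, a batch is randomised once enough participants "have completed their baseline assessments". Assignment to a program follows. The schedule of assessments (Table 2) has the MADRS at enrolment, baseline and week 8, so week 8 is the only MADRS taken after groups exist.
- **Sample size.** "An Intraclass Correlation Coefficient = 0.2 was used to account for variation between therapy groups with an average size of 8 per group". The inflation is applied to a sample size derived from a standard deviation "of change in MADRS scores from baseline to week 8 = 3.6 (baseline variance = 4.03"). The clustering is therefore budgeted on the change scale.

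**The concern.** A therapy group can make its members' scores alike only once it has met. The listed hierarchy instead places group above every measurement, including baseline. If each level contributes a random intercept, the group term is the same number at baseline and week 8, and subtracting one from the other removes it. The model can then estimate a group variance and still give the primary contrast a standard error close to that of an unclustered comparison.

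In a non-inferiority trial an interval that is too narrow errs in the harmful direction: its upper limit falls below 1.6 too often, and a therapy that is inferior by the full margin is declared non-inferior too often.

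**Working it through.** **Inputs from the Sample size section.** Margin: "therefore the non-inferiority margin was set at < 1.6". SD of change 3.6, ICC 0.2, 8 per group. Attrition: "A conservative level of attrition = 20% was further assumed". Final size 378, or 189 per arm (189/8, about 24 groups per arm).

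**Assumptions.** Alpha, sidedness, power and the true difference used for planning are not stated. The ICC is taken to apply to the change score in both arms.

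**1. Reproduce the plan's figure.** n per arm = 2(z₁₋α + z₁₋β)²·SD²/margin². With one-sided 5%, 80% power and a true difference of 0: 2 × (1.645 + 0.842)² × 3.6²/1.6² = 62.6, so 63 per arm, matching "resulting in a total sample size of 126". Other standard pairs do not match: 2.5%/80% gives 160, 5%/90% gives 174 and 2.5%/90% gives 214. The design effect is 1 + 7 × 0.2 = 2.4, and 126 × 2.4/0.8 = 378.

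**2. Standard error that the plan budgets for.** 378 × 0.8 = 302.4 analysed, 151.2 per arm. 3.6 × √(2/151.2) × √2.4 = 0.64.

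**3. Cancellation.** With random intercepts, a score is fixed effects + u(group) + v(participant) + e(occasion). Week 8 minus baseline leaves fixed effects + e₈ − e₀; u and v are gone. A generalised least squares check with 24 groups of 8 per arm and complete pairs gave an arm-by-time SE of 0.3674 at group variances of 0, 1, 3 and 6, equal to the unclustered 3.6 × √(2/192). With 20% missing at week 8 it was 0.39-0.40.

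**4. True standard error at ICC 0.2.**
- Complete groups of 8: 0.3674 × √2.4 = 0.57.
- After 20% attrition (6.4 per group, design effect 1 + 5.4 × 0.2 = 2.08): 3.6 × √(2/153.6) × √2.08 = 0.59.

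**5. False non-inferiority at a true difference of 1.6.** If the group effect is lost, the rate is Φ(−z₁₋α/√DEFF). The simulation used 1,000 trials per setting, REML, 24 groups of 8 per arm, 20% missing at week 8, a group effect arising after baseline, and normal critical values. Its range covers the planning value 4.03 read as a baseline variance (as printed) and as an SD.

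| ICC 0.2 | nominal 5% | nominal 2.5% |
|---|---|---|
| Random intercepts, formula | 12.7-14.4% | 8.7-10.3% |
| Random intercepts, simulation | 15.2-15.8% | 10.3-11.0% |
| Group effect added at week 8, simulation | 5.3-5.5% | 2.3-3.1% |

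In the simulation the random-intercept model reported a mean SE of 0.39-0.40 while the estimates had an SD of 0.61. With the week-8 group effect the mean SE was 0.61-0.63. Constraining the arms to equal baseline means does not help: random intercepts then gave 16.6-19.2% at nominal 5%.

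**6. Dependence on the ICC.** At ICC 0.05 and nominal 5%, the formula gives 7.2-7.8% and the simulation 8.0%. By the formula, doubling from 5% needs an ICC of about 0.09 (8 per group) to 0.12 (6.4 per group). The simulation's standard error is about 1.1 points near 15% and 0.7 points near 5%. At ICC 0 the random-intercept model gave 6.1%, so about one point of its rates need not be due to clustering.

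**The case against.** The strongest reply is that the article never says random intercept. It lists levels, and a three-level model with a group-level random effect on time fits the same words and holds its error rate (last row of the table). Random-effects structure is commonly left to an analysis plan, and none is shown. The intent is also plain: the design is named as an individually randomised group treatment trial, the sample size is inflated by 2.4, and group is in the model.

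Much of this stands. A reader might infer that the plan ignores clustering, or that its false non-inferiority rate will more than double. The documents support neither as a flat statement: the first depends on a random structure that the article leaves open, the second on that and on the ICC. Nor is the unclustered standard error reproduced exactly once there is dropout. The planned pattern-mixture imputation was not simulated. A reader might also want the randomisation batch added to the model. The documents give no variance for it, and its omission is not what causes the error shown here, so it forms no part of this point.

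What does not stand is that the wording is harmless. It nests baseline scores in groups that did not yet exist, mentions no effect confined to follow-up, and is most naturally fitted with one random intercept per level.

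**Conclusion.** The point holds conditionally. If level 3 is a random intercept only, the primary interval omits nearly all of the clustering: it rests on a standard error of about 0.40 where the true value at ICC 0.2 is about 0.6. False non-inferiority is then 13-16% at nominal one-sided 5%, about 2.5 to 3.2 times nominal, or 9-11% at 2.5%, about 3.5 to 4.4 times. With a smaller ICC the inflation is smaller.

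The result rests on the plan's own ICC of 0.2 applying to change scores in both arms, on equal groups of 8 (the article allows 4 to 10), and on an alpha inferred from the sample size. Because two readings of one sentence differ about threefold in the error rate of the primary claim, the choice should be fixed in writing before the final data are analysed.

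**What to change.** State one of the following as the primary model:

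1. The longitudinal model with the therapy-group random effect acting at follow-up only, that is, a group-level random effect on time or week 8 and none at baseline.
2. Week-8 MADRS on arm, adjusted for baseline MADRS, with a random intercept for therapy group.

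In either case name a small-sample degrees-of-freedom correction, since there are only about 48 groups in total, and use the same structure for the secondary outcomes.

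The change is to analysis wording only and needs no new data or participants. The interval becomes wider, with a standard error of about 0.6 instead of 0.4. That is within the 0.64 implied by the plan's own inflation, so the power for which 378 was chosen is kept.
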